##### Pharmacy staff training

All pharmacy staff of the intervention group will be invited to participate in three face-to-face meetings as a complement to the virtual course for the proper utilization of drugs with fiscalized substances. Each meeting will last 4 h, for a total of 12 h of face-to-face training. Each pharmacist will make their presentation according to the topics programmed in each training meeting: (a) training 1, feedback from modules 1 and 2 of the virtual course; (b) training 2, feedback from modules 3, 4, and 5 of the virtual course; and (c) training 3, feedback from modules 6 and 7 of the virtual course. Lectures will be prepared in PowerPoint presentations, videos, and practical activities such as role-playing and case presentation. The pharmacists who will conduct the face-to-face meetings are professional pharmacists, with experience in teaching and research in the specific topics and a strong background in clinical and therapeutic pharmacy. The professional pharmacists are also co-authoring the virtual course modules.

#### Control group

Due to the nature of the study, there will be no blinding since the pharmacy staff of drugstores and drugstores/pharmacies that meet the inclusion criteria will be informed about the study and will register after their signed authorization. Pharmacy staff in the control group will receive written material on the correct use of complex pharmaceutical forms, with information that focuses on the importance of providing this information to patients and caregivers to achieve the goals of treatment. Randomization will take place at baseline. The written material will be delivered during the follow-up time.

### Criteria for discontinuing

When pharmacy staff leave or change their place of work to the original one where they were initially randomized in the study or decide voluntarily to withdraw from the study, it will be considered as a criterion for discontinuing.

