## Trial design

A multicenter, prospective, parallel-group, cluster-randomized controlled, superiority trial will be conducted (see Figs. 1 and 2). The study will be carried out over 12 months (1 year) of intervention (i.e., the continuing education program) delivery and follow-up. Drugstores and drugstores/pharmacies (the clusters) will be randomized at a 1:1 ratio to enroll in either the intervention group or the control group. The geography zone (neighborhoods) will be randomized stratified.

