##### Pharmacy staff

The study will recruit at least one pharmacy staff member from each drugstore or drugstore/pharmacy (professional, technological, technical, or Drug Dealer). To be included in the study, the pharmacy staff will have to meet the following criteria: (a) work in the drugstores or drugstores/pharmacies and (b) have access to a computer and the Internet.

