### Sample size

A study carried out in Spain evaluated the competences pharmacists, principally the knowledge before and after an educational intervention facilitated by pharmacists, finding that the intervention increases in 37% the knowledge of the pharmacists who attended the course [23]. Therefore, the continuing education program is expected to improve the pharmacy staff competencies in the intervention group at least 30% and in the control group by 15% (less in improving or increasing competencies). With a confidence level of 95% and a power of 80% and superiority design, it was calculated that it is necessary to include at least 121 drugstores or drugstores/pharmacies in each group. To cover losses to follow-up, the sample was increased by 10%, increasing the sensitivity for the fulfillment of secondary objectives; the size of the final sample will be 135 drugstores or drugstores/pharmacies for each group (1:1 ratio).

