##### Virtual course

The virtual course will be composed of 7 modules. The study time for each module will require an average of 20 h of study (ten synchronous hours and ten asynchronous hours). Each module will be structured as follows: (a) initial evaluation,( b) development of themes and content, and (c) final evaluation. The virtual course will be designed using Moodle 3.3.2+, which is a Learning Management System (LMS) for the development, administration, and documentation of learning. The virtual course will have a combination of different multimedia tools such as audios (locutions), videos with experts, animated videos, animations, videocasts, infographics, and interactive tests with drag and drop exercises, association, completion, and multiple selection responses.

The development of the virtual course will not be carried out in a synchronized manner among all subjects. Therefore, the course will be carried out in a staggered way; that is, the seven modules will be activated systematically 1 to 7, on average, every 45 to 60 days. These modules constitute a refresher course in knowledge, and those who complete all the modules of the virtual course will be certified by the University of Antioquia. It will be established as an actualization course.

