#### Level of satisfaction of patients or caregivers with the ambulatory (outpatient) pharmacy services

A questionnaire will be constructed from the requirements of Colombian pharmaceutical regulations and different bibliographical references [39, 40] to evaluate the information and education services on the appropriate use of drugs. The questionnaire will inquire about the following: (1) establishment information, (2) patient or caregiver information, (3) medication information, (4) assessment of the information and education service, and (5) qualification of the care received. The satisfaction of the care received in drugstores or drugstores/pharmacies will be evaluated with a 5-point scale ranging from excellent, very good, good, satisfactory, regular, and bad

To promote the retention of participants and complete follow-ups, the pharmacy staff will receive a physical certificate when he/she completes each module of the virtual course, which is part of the intervention (intervention group). Additionally, at the end of the follow-up time, all pharmacies of the intervention and control groups will receive a physical certificate that guarantees that said establishment participated in the study.

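### A job change is handled like withdrawal from the study, which can leave a randomised pharmacy without primary T12 data, possibly unequally by arm

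*Protocol article*

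**What the plan says.** All places are in the Protocol article.

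- **Unit of randomisation.** Trial design: "Drugstores and drugstores/pharmacies (the clusters) will be randomized at a 1:1 ratio".
- **Participants per pharmacy.** Pharmacy staff (inclusion criteria): "The study will recruit at least one pharmacy staff member from each drugstore or drugstore/pharmacy". One is the minimum and no maximum is given.
- **Discontinuation.** Criteria for discontinuing is one sentence with two triggers. The first is "When pharmacy staff leave or change their place of work to the original one where they were initially randomized in the study". The second applies to staff who "decide voluntarily to withdraw from the study, it will be considered as a criterion for discontinuing". The sentence speaks of staff as the randomised party. It does not say whether the intervention, the person's follow-up or the pharmacy's participation is discontinued.
- **Primary outcome.** Outcomes: staff complete two questionnaires themselves at T0 and T12, and simulated-patient visits take place at the same two times.
- **Loss allowance.** Sample size: 121 pharmacies per group, then "To cover losses to follow-up, the sample was increased by 10" per cent, giving 135. The allowance is counted in pharmacies and is the same in both groups.
- **Workload.** Virtual course: seven modules, and "The study time for each module will require an average of 20 h of study". Pharmacy staff training: three meetings of 4 h. Control group: written material only. Recruitment: staff are not paid.
- **Retention.** In the intervention group only, "the pharmacy staff will receive a physical certificate when he/she completes each module of the virtual course". Telephone calls go to both groups, and every pharmacy in both groups receives a participation certificate at the end.

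**The concern.** A job change and a refusal to continue are different events. Someone who changes employer has not withdrawn consent and may still be reachable, and the randomised pharmacy is still there to be visited. The discontinuation sentence gives both events the same consequence. If that consequence is the end of follow-up, a pharmacy with one participant contributes no primary questionnaire at T12, although it was randomised and measured at T0. A successor cannot fill the gap in the paired comparison, because the McNemar tests named under Statistical methods need T0 and T12 from the same person. An analysis plan can define populations and missing-data methods, but it cannot restore questionnaires that were never collected.

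What is at stake is comparability. The two arms make very different demands on staff and offer different incentives to stay. If the intervention arm loses more people, and those people would have improved less, the programme looks better than it is.

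**Working it through.** **1. The plan's own figure.** Inputs from Sample size: "improve the pharmacy staff competencies in the intervention group at least 30% and in the control group by 15" per cent, 95% confidence, 80% power. I read these as the proportions improving, with a two-sided 5% test, pooled variance and no continuity correction:

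n = [1.960 × √(2 × 0.225 × 0.775) + 0.842 × √(0.30 × 0.70 + 0.15 × 0.85)]² / 0.15² = (1.157 + 0.489)² / 0.0225 ≈ 120.5, so **121**.

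Allowance: 121 / (1 − 0.10) = 134.4, so **135**. Both stated figures reproduce.

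**2. Workload contrast.** 7 × 20 h = 140 h, plus 3 × 4 h = 12 h, gives **152 h**. The control group reads written material, for which no hours are given.

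**3. Power under unequal loss.** The loss rates are assumptions; the article gives none by arm. Start from 135 per arm, keep 30% v 15% and, like the article's calculation, make no clustering adjustment.

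| Loss, intervention / control | Remaining | Power |
|---|---|---|
| 10% / 10% | 121.5 / 121.5 | 0.80 |
| 20% / 5% | 108 / 128.25 | 0.79 |
| 20% / 10% | 108 / 121.5 | 0.78 |
| 30% / 10% | 94.5 / 121.5 | 0.76 |
| 40% / 10% | 81 / 121.5 | 0.72 |

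**4. Bias with no true effect.** Assume 15% improve in both arms and control loss is unrelated to outcome, so the control rate stays at 15%. If a fraction L of the intervention arm is lost and those lost would have improved at rate q, the observed intervention rate is

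(0.15 − L × q) / (1 − L).

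At L = 0.20:

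- q = 0 (only non-improvers are lost): 0.15 / 0.80 = 18.75%, a false difference of **3.75, about 3.8 points**.
- q = 7.5% (those lost improve at half the rate): (0.15 − 0.015) / 0.80 = 16.9%, a false difference of **1.9 points**.
- q = 15% (loss unrelated to outcome): 15%, a false difference of **zero**.

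With q = 0 and L = 10%, 30% and 40%, the false difference is 1.7, 6.4 and 10.0 points. With 10% control loss, the chance of a significant result favouring the programme at L = 10%, 20%, 30% and 40% is about 5%, 12%, 23% and 43%, against a nominal 2.5%.

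Unequal loss on this scale costs little power. The exposure is to bias, and the 10% allowance does nothing about that.

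**The case against.** The discontinuation sentence does not say that the pharmacy is removed or that T12 data are not collected. It stands between the description of the interventions and the section on adherence to them, so it can be read as ending the intervention only. That would already be close to what is asked for here. A reader might infer that randomised pharmacies are dropped, but the text does not support this. A pharmacy may have more than one participant, and simulated-patient visits and patient interviews can still be done there.

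A reader might also infer that completers of a long course will be compared with nearly all controls. That does not follow either. The two triggers are leaving or changing the job and withdrawing from the study. Stopping the course, or finishing only some modules, is neither.

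Unequal loss is an inference. No rate by arm is given, a job change need not depend on allocation, and the 152 h are spread over about a year because modules open every 45 to 60 days on average. The calls and the end-of-study certificate reach both arms. The module certificates may help retention in the intervention arm or make a job move easier.

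The skills and attitudes questionnaire asks how often tasks are performed, so it may not be answerable by someone who has left pharmacy work. A simulated-patient visit after a departure may assess an untrained successor.

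All of this stands, and it limits the point to an ambiguity that should be closed. What remains is that the sentence joins a job change to withdrawal from the study and calls staff randomised where pharmacies are. The article does not say that leavers are still measured at T12.

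**Conclusion.** The point holds as a defect in a stated follow-up rule. Read as ending follow-up, the rule can leave a randomised pharmacy without its primary T12 questionnaires. The workload contrast makes unequal, outcome-related loss plausible but not documented.

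The size rests on assumed figures. At 20% intervention loss the false difference runs from zero (loss unrelated to outcome) to about 3.8 points (only non-improvers lost), against a planned difference of 15 points. The upper figure is an unfavourable case, not a forecast. Power is a minor matter: a reader might conclude that loss above 10% in one arm destroys it, but it stays at 0.78 to 0.79 under 20%/10% or 20%/5% loss.

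The absence of an analysis population or a missing-data method from the article is not part of this point, since a fuller protocol or analysis plan may contain them. The change is worth making because it is cheap and because uncollected data cannot be replaced later.

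**What to change.** Reword Criteria for discontinuing so that it separates the two triggers and names the pharmacy as the randomised unit:

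- A job change ends the intervention at most, not follow-up.
- The T12 knowledge questionnaire is sought from the enrolled person wherever they now work, and the skills and attitudes questionnaire if they are still in pharmacy work, unless they withdraw consent for data.
- The planned T12 simulated-patient visit and patient interviews go ahead in the randomised pharmacy, with a record of whether the enrolled participant still works there.
- Every pharmacy and participant stays in the assigned arm.

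The cost is some extra telephone or mail contact with leavers; the pharmacy visits are already planned. The estimate will then reflect offering the programme, and may be smaller than the effect among those who stayed. If T12 collection has already closed, report by arm how many participants changed job, how many withdrew, and which of them were measured.

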### Strategies to improve adherence to intervention protocols

The pharmacy staff in both groups will receive phone calls from one of the researchers to encourage compliance with the protocol. The pharmacy staff of the study will not be blinded to the assignment of the intervention, and the same researcher will visit both groups. The researcher will visit all drugstores and drugstores/pharmacies to train and provide technical support to the pharmacy staff of the intervention group in the access and use of the virtual classroom and the virtual course. During the 12 months that the monitoring and intervention will last, one of the researchers will be available to receive telephone calls to solve doubts and academic concerns and provide technical support related to the virtual classroom and the virtual course. Telephone calls have several purposes: (1) accompany pharmacy staff during the study and promote adherence to the continuing education program for their development, (2) accompaniment and technical support in the use of the educational platform, and (3) promote communication to invite pharmacy staff to face-to-face training sessions to be scheduled to complement their training.

### Outcomes

Pharmacy staff competencies (knowledge, skills, and attitudes) will be assessed using two self-applied questionnaires. The measurements will be performed at baseline (T0) before the intervention and 12 months (1 year) after completing the follow-up (T12). Additionally, the simulated patient technique will be used to evaluate the skills and attitudes of the pharmacy staff in the dispensation and the information supply for the correct use of drugs (T0 and T12).

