## Objectives

The primary objective is to evaluate the effectiveness of a continuing education program to improve pharmacy staff competencies (knowledge, skills, and attitudes) to improve the ambulatory (outpatient) pharmacy services: dispensation, health education, and pharmacovigilance of drugs with fiscalized substances (including controlled drugs). The secondary objective is to characterize the processes associated with the utilization of drugs with fiscalized substances (including controlled drugs) and regulation compliance and the degree of implementation of ambulatory (outpatient) pharmacy services. The third objective is to evaluate the satisfaction of patients and caregivers with ambulatory (outpatient) pharmacy services. The fourth objective is to evaluate the satisfaction level of pharmacy staff with the provided educational program.

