#### Community pharmacy staff competencies (knowledge, skills, and attitudes)

For the measurement of knowledge, a self-applied questionnaire of 50 multiple-choice questions (4 possible answers) with only one answer was constructed, and it will be categorized as correct or incorrect. The questionnaire will have the following topics: (1) pharmaceutical terminology and basic pharmacology, (2) pharmaceutical legislation, (3) technical and administrative management of the pharmacy, (4) communication and health education from the pharmacy, (5) good practices of dispensing and proper use of medicines, (6) pharmacovigilance from the pharmacy, and (7) pharmaceutical intervention on some common diseases in pharmacy (depression, anxiety disorder, sleep disorders, and pain management).

For the measurement of skills and attitudes, a self-applied questionnaire of 100 questions or performance criteria was constructed, which will be evaluated according to the frequency in which it will perform. For this purpose, a Likert scale will be established with four possible options: never (1), sometimes (2), usually (3), or always (4) that evaluate the following competencies—(a) provision of patient care: initial contact with the patient, medical prescription, medication needs, medication reconciliation, medication supply, use of guidelines and protocols, drug specifications, drug interactions, information about medications and patient education, additional activities, identification of drug-related problems, patient care, and evaluation of results; (b) personal: personal organization, practical communication skills, teamwork, and professionalism; (c) problem-solving: access related to information, knowledge, information analysis, and monitoring the patient; and (d) management and organization: clinical management and pharmacological safety, service provision, acquisition, and satisfaction of the services offered.

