### Statistical methods

Baseline and demographic characteristics will be analyzed descriptively. All primary and secondary outcomes will be compared in pre-post analyses and between-group comparisons. Comparisons for categorical variables will be conducted by using the chi-square test (or the Fisher exact test when appropriate). For continuous variables, we will use the independent sample *t* test (if the distribution is not normal, we will use the Mann-Whitney *U* test). Student’s *t* test will be used to compare means and odds ratios (ORs), and 95% confidence intervals (CIs) will be estimated as well. ORs will be used with the data reported from the knowledge questionnaire, to establish the association between receiving or not receiving the intervention and improving or not knowing. Spearman’s correlation will be used to identify the association for test and re-test reliability. Multivariable analyses will be performed to explain the association of multiple variables with the factors significantly related to the primary outcome (such as the job profile of the pharmacy staff, and others that will be considered as relevant variables). The McNemar tests will be used to analyze the difference in scores of the competency’s questionnaire of skills and attitudes and the scores of the knowledge questionnaire. All statistical tests will be computed using the Statistical Package for the Social Sciences (version 23; SPSS, Chicago, IL, USA) with significance defined as a *p* < 0.05.

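### Three instruments serve the primary objective, but none is named as the primary endpoint and no rule says which must succeed, while the sample size covers one 5% comparison

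*Protocol article*

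**What the plan says.** The Objectives section defines the primary objective as improving competencies, a construct with three parts: knowledge, skills and attitudes. The Outcomes section, which stands apart from the list of secondary outcomes, assigns three measures to it at T0 and T12.

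- Two questionnaires: "Pharmacy staff competencies (knowledge, skills, and attitudes) will be assessed using two self-applied questionnaires". The section on competencies describes the knowledge test as "a self-applied questionnaire of 50 multiple-choice questions (4 possible answers) with only one answer was constructed" and the skills and attitudes instrument as "a self-applied questionnaire of 100 questions or performance criteria was constructed", answered on a four-point frequency scale.
- A simulated-patient visit: "Additionally, the simulated patient technique will be used to evaluate the skills and attitudes of the pharmacy staff".

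The Statistical methods section compares every primary and secondary outcome both pre-post and between groups. It adds odds ratios for improvement on the knowledge questionnaire and McNemar tests for both questionnaires. All tests are computed "with significance defined as a *p* < 0.05".

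The Sample size section plans "With a confidence level of 95% and a power of 80% and superiority design" and expects competencies to improve by at least 30% in the intervention group and by 15% in the control group. It does not say on which instrument. It starts from a Spanish study that principally measured knowledge.

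The Discussion says that the components of competence should be evaluated jointly, but attaches no decision rule to that word.

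**The concern.** The article names no primary score, composite or testing order, and does not say whether one instrument or all three must succeed. The trial is sized for one test, yet at least three between-group results could be read as the answer to the primary question. If they disagree, nothing written beforehand decides what the trial has shown.

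The instruments also differ in how open they are to bias. The skills and attitudes questionnaire asks unblinded staff how often they perform each criterion, and trained staff may know the desired answer. In the simulated-patient visit, staff are not to know that the patient is not real. A conclusion about skills could therefore rest on either source, and the choice could be made after seeing both.

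**Working it through.** **1. The plan's own figure.** Inputs from the Sample size section: 30% and 15%, 95% confidence, 80% power, 1:1 allocation, 10% losses. Read as a two-sided comparison of two proportions with pooled variance and no continuity correction:

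n = [1.960 × √(2 × 0.225 × 0.775) + 0.842 × √(0.30 × 0.70 + 0.15 × 0.85)]² / 0.15²

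= (1.157 + 0.489)² / 0.0225 ≈ 120.5, so **121 per group**.

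Losses: 121 / 0.90 = 134.4, so **135 per group**. Both stated figures are reproduced. They correspond to one binary contrast at one two-sided 5% test. That the percentages are proportions of improvers is inferred from this match; the article does not define improvement.

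**2. If success on any one instrument counts.** Assumptions: one between-group test per instrument, three tests, each two-sided at 0.05. Under independence:

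1 − 0.95³ = 1 − 0.8574 = **14.3%**, or 2.85 times 5%.

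For false findings favouring the program only: 1 − 0.975³ = 7.3%, against a nominal 2.5%.

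The article gives no correlation between the test statistics, so a range is shown. Results for correlations above 0 come from 2 million simulated draws of three equally correlated normal statistics.

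| Assumed correlation | Any of three, two-sided | Multiple of 5% | Favouring the program only (nominal 2.5%) |
|---|---|---|---|
| 0 | 14.3% | 2.85 | 7.3% |
| 0.3 | 13.6% | 2.7 | 6.8% |
| 0.5 | 12.5% | 2.5 | 6.2% |
| 0.7 | 10.9% | 2.2 | 5.4% |
| 0.9 | 8.3% | 1.7 | 4.2% |

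**3. If all three must succeed.** The chance that all three are falsely significant cannot exceed 5%, so there is no inflation. Power falls instead. For illustration only, suppose each test has 80% power; the article gives power for one contrast and not per instrument. Joint power is then 0.80³ = 51% under independence, and rises towards 80% only as the correlation approaches 1.

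**4. Cost of splitting alpha.** Three tests at 0.05 / 3 = 0.0167, with the same formula, need 161 per group, or 161 / 0.90 = 178.9, so 179 after losses. At that level, power for 30% against 15% is 66% with 121 per group and 71% with 135.

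**The case against.** **The statistical analysis plan is not shown, and this is a condensed article.** Testing order and multiplicity method are commonly left to such a plan, so their absence alone is no finding. That stands. The identity of the primary endpoint is different: it belongs in the protocol and determines what the sample size means. The article also states a rule of its own, 5% for every test.

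**There may be only two primary instruments.** The simulated patient is introduced as an addition and could be supportive. With two tests, any-of-two error is 1 − 0.95² = 9.75% under independence and about 7% at a correlation of 0.9. The article does not settle which reading applies, so the gap remains.

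**Joint evaluation points away from any-one-wins.** This is fair. The Discussion's wording leans towards considering the components together, but gives no rule that could be applied to three p-values.

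A reader might also infer stronger points that the article does not support:

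- *A false claim of effectiveness is about three times as likely as it should be.* This needs three independent tests and success on any one, and the article states neither. The same staff are assessed on related competencies, so positive correlation is likely. The 14.3% also counts false findings in both directions.
- *The knowledge odds ratio is a fourth test, giving 1 − 0.95⁴ = 18.5%.* It reuses the knowledge questionnaire data, so it cannot be treated as independent.
- *The simulated patient should override self-report.* It covers one tramadol and back-pain scenario, whereas the questionnaire has 100 items across patient care, personal, problem-solving and management domains. The two overlap only in part. A researcher accompanies the simulated patients, and the article does not say that they are blinded to allocation.

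**Conclusion.** The point holds as an unfixed primary endpoint and success rule. Following the article as written leaves the primary claim open to choice after the results are known, and leaves the 30% against 15% assumption attached to no instrument.

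The size depends on a rule that the article does not give. If any of three counts, two-sided familywise error is up to about 14%, and about 8% to 14% for correlations of 0.9 to 0.3. If all three must succeed, there is no inflation but a loss of power. The error figures rest on one between-group test per instrument. Pre-post and other planned tests could raise them if they counted towards the claim, but the article does not say that they would. This should be corrected; it does not undermine the design.

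**What to change.** Before analysis, make these changes in Outcomes, Sample size and Statistical methods:

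1. Name one primary endpoint. The between-group comparison of improvement on the knowledge questionnaire at T12 is the natural choice, because the source study for the sample size principally concerned knowledge and the planned odds ratio uses the knowledge data. Define what counts as improved, and state that 30% against 15% refers to this endpoint.
2. Test the simulated-patient score and then the self-rated skills and attitudes score, in that fixed order, each at 5% and only if the previous test succeeds.
3. Treat pre-post and other comparisons as supportive, reported with confidence intervals.
4. Report simulated-patient and self-report results side by side, note that self-report is unblinded, and let neither override the other.

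The cost is a few lines of text, and 121 and 135 per group stay as they are. The downside is that later instruments can be claimed only if the earlier ones succeed. Fixed order is preferable here to dividing alpha across the three, given the loss of power or larger sample shown above. The Trial status section describes the trial as still in intervention and follow-up, so on that description the choice can be made before the results are known.
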